## Abstract

**Background:**

Social anxiety disorder (SAD) is highly prevalent among university students, but the majority of affected students remain untreated. Internet- and mobile-based self-help interventions (IMIs) may be a promising strategy to address this unmet need. This study aims to investigate the efficacy and cost-effectiveness of an unguided internet-based treatment for SAD among university students. The intervention is optimized for the treatment of university students and includes one module targeting fear of positive evaluations that is a neglected aspect of SAD treatment.

**Methods:**

The study is a two arm randomized controlled trial in which 200 university students with a primary diagnosis of SAD will be assigned randomly to either a wait-list control group (WLC) or the intervention group (IG). The intervention consists of 9 sessions of an internet-based cognitive-behavioral treatment, which also includes a module on fear of positive evaluation (FPE). Guidance is delivered only on the basis of standardized automatic messages, consisting of positive reinforcements for session completion, reminders, and motivational messages in response to non-adherence. All participants will additionally have full access to treatment as usual. Diagnostic status will be assessed through Structured Clinical Interviews for DSM Disorders (SCID). Assessments will be completed at baseline, 10 weeks and 6-month follow-up. The primary outcome will be SAD symptoms at post-treatment, assessed via the Social Phobia Scale (SPS) and the Social Interaction Anxiety Scale (SIAS). Secondary outcomes will include diagnostic status, depression, quality of life and fear of positive evaluation. Cost-effectiveness and cost-utility analyses will be evaluated from a societal and health provider perspective.

**Discussion:**

Results of this study will contribute to growing evidence for the efficacy and cost-effectiveness of unguided IMIs for the treatment of SAD in university students. Consequently, this trial may provide valuable information for policy makers and clinicians regarding the allocation of limited treatment resources to such interventions.

**Trial registration:**

DRKS00011424 (German Clinical Trials Register (DRKS)) Registered 14/12/2016.

## Background

Anxiety disorders have the highest prevalence compared to other mental health disorders, showing an estimated lifetime prevalence of 10–22% in European Countries [1]. Social anxiety disorder (SAD) is ranked as the third most common anxiety disorder in Germany [2], and the prevalence estimates of SAD in university students range from 3.4% (12-month) in the United States [3] to 16.1% (point-prevalence) in Sweden [4].

SAD among university students has been associated with a number of adverse effects, including low quality of life [5] and problems with identity formation [6], increased consumption of alcohol [7] and high levels of suicidal ideation [8]. Additionally, SAD-related emotional distress causes dysfunctional avoidance strategies, which are associated with underachievement and may lead to premature drop out from university [4]. Therefore, the economic burden extends beyond the direct costs of treatment to indirect costs (e.g. low productivity, increased number of sick days, lower qualification level [9, 10]) and intangible costs (e.g. reduced quality of life, social impairment). Thus, treatment of SAD is of particular interest to the public healthcare system and health services in and outside of university [11, 12], especially as SAD may become a chronic condition when left untreated [13].

Effective treatment options exist [14, 15], but are only used by a small proportion of those in need [16, 17]. Reasons for low treatment rates include not only a limited availability of trained clinicians but also other barriers to help-seeking such as fear of stigmatization. Fear of negative evaluation, the expectation that others might judge one’s behavior or physical symptoms as embarrassing or humiliating, [18, 19] is the key feature of SAD. Hence, the nature of SAD is one major reason which prevents university students from seeking professional advice [9, 20].

Internet- and mobile-based interventions are a promising strategy to reach underserved SAD populations. In contrast to traditional face-to-face therapy IMIs are immediately accessible, lack stigmatization, are more flexible, anonymous, and initiated with minimal (or no) human contact [21–23]. In addition, although the initial costs of developing an IMI can be quite high, the low marginal costs of providing IMIs to additional user are assumed to lead to lower overall expenditures [24]. Moreover, IMIs are likely to reduce health care delivery costs compared to face-to-face treatment, as IMIs involve minimal or no contact with mental health care specialists and also reduce travel costs.

A large number of studies have shown that IMIs can be effective in the treatment of common mental disorders [22]. The most recent systematic review on IMIs for SAD showed a mean standardized effect size of g = 0.84 [0.72–0.97] compared to untreated control groups and g = 0.38 [0.13–0.62] compared to active control conditions [25]. We are aware of only one small study (*n* = 38) that evaluated a psychological internet supported intervention for SAD in university students [26]. This study assessed an internet-based self-help intervention with minimal email contact to a psychotherapist with in vivo group exposure compared to no in vivo group exposure. The intervention resulted in large pre-post within-group effect-sizes for both groups. The generalizability of these results are, however, limited due to methodological shortcomings (e.g. small sample size). In addition, the study did evaluate neither the cost-effectiveness of the intervention nor the effects of unguided self-help.

One of the major cost-drivers and potential barriers for large-scale treatment dissemination is the provided level of therapeutic guidance in IMIs. In a recent meta-analysis guided IMIs yielded a mean average effect of g = 0.87 [0.72–1.02] compared to passive control conditions such as WLC (*n* = 11) [25]. The standardized effect size of unguided IMIs was g = 0.78 [0.50–1.05] compared to passive controls (*n* = 8). The effect sizes (0.28–1.47) varied widely between unguided IMIs [27–34], which makes it difficult to anticipate the expected effect size for future studies. We suspect that the variance in effect sizes between studies could be explained by methodological differences such as small (*n* = 20–40) [27, 29–32] to moderate (*n* = 56–62) [28, 34] sample sizes, different lengths of follow-ups (e.g. only three studies evaluated long-term effects [27–29]) and high dropout rates. Therefore, additional research is needed to determine the efficacy of unguided internet-based interventions in the treatment of SAD, particularly among university students.

Although it is often assumed that IMIs tend to be cost-effective, there is limited empirical evidence showing the impact on health economic outcomes [35–37]. To the best of our knowledge, only three studies investigated the cost-effectiveness of IMIs for SAD; all of these studies evaluated a therapist guided IMI [38–40]. To date, no study has investigated the cost-effectiveness of an internet-based intervention in university students, and no study has evaluated the health economic effects of an unguided internet-based intervention for SAD.

Although the efficacy of Cognitive Behavioral Therapy (CBT) in the treatment of SAD is well-documented, there is still room for improvement. Recent findings suggest not only fear of negative evaluations to be a central feature of SAD, but also prove a strong link between SAD and the fear of positive evaluation (FPE) [41, 42]. According to Weeks and Howell’s (2012) bivalent fear of evaluation model of social phobia, fear of evaluation in general is the core component of SAD, including the fear of negative (FNE) and positive evaluation [43]. The function of FPE in SAD also has been discussed in the context of evolutionary models of social anxiety [44]. Empirical evidence shows that FPE and FNE are related but distinct factors contributing to SAD, with FPE explaining a unique and independent proportion of variance in the fear of social interactions [45]. Even though established treatments for SAD do not address FPE directly, there is evidence that CBT can reduce FPE, albeit with smaller effect sizes compared to FNE [42]. And, importantly, neglecting FPE in SAD treatments may impede treatment progress (e.g., when clients still feel anxious after successful exposures that received positive feedback) [46]. Specifically, people who endorse FPE do not feel proud when making progress or achieving goals and, paradoxically, often experience discomfort [41]. In that sense, FPE often results in socially anxious people avoiding social situations in which they are the focal point (e.g., group work, presentations at university) which prevents their exposure to positive social feedback and safeguards their social status within the group [42, 47]. Although research has shown that FPE is responsive to cognitive-behavioral therapy [48], no intervention has systematically addressed this as a treatment component of SAD.

The aim of this study will be to evaluate whether an unguided internet-based intervention for SAD is effective in reducing social anxiety symptoms and other secondary outcomes such as depression, fear of positive evaluation, interpersonal problems and quality of life when compared to a WLC in university students. Additionally, cost-effectiveness analyses will be conducted from societal and health provider perspective in order to examine whether this internet-based intervention for SAD represents good value for money.

This study is part of the recently launched Caring Universities – the World Health Organization (WHO) World Mental Health International College Student (WMH-ICS) initiative (https://www.hcp.med.harvard.edu/wmh/college_student_survey.php) [49, 50]. It is an international initiative which aims to obtain accurate cross-national data on the prevalence, and correlates of mental disorders among university students throughout the world, assess unmet needs for treatment, develop practical methods to improve mental health intervention utilization, and evaluate effective strategies for the prevention and treatment of mental health disorders in university students.

## Methods

### Study design

This study is a randomized-controlled trial in which the assumed superiority of an internet-based intervention for SAD is evaluated compared to a WLC. The intervention group will receive the internet-based self-help treatment for social anxiety and the control group will obtain access to this intervention after 6 months. Both conditions have full access to university and community treatment as usual.

### Participants

We anticipate recruiting a total of *N* = 200 participants of which 100 participants will be assigned to each of the two conditions. Participants will be recruited in Germany, Austria and Switzerland. The recruitment strategy consists of various components: a study website, a promotional video, postings to Facebook and Internet forums and an email with information of the study sent to all German, Swiss and Austrian university psychological counseling centers and all students attending different universities based in Ulm, FAU, Bern, Dresden, Hagen, and Vienna. The study flow is illustrated in Fig. 1.

**Fig. 1 Fig1:**
[figure not shown]
Study flow chart

### Inclusion criteria

Participants will be included if theyare a student,are at least 18 years old,have internet access,have sufficient German language skills as assessed via self-report (“Do you speak and understand German?”),exceed predefined cut-off scores in the SPS or SIAS,fulfill the diagnostic criteria of SAD according to DSM-IV assessed via a SCID-I diagnostic interview,have the ability to provide a written informed consent.

### Exclusion criteria

Participants will be excluded if they,show an acute suicidal risk according to the suicide item of the Beck Depression Inventory II (BDI II) (score > 1) or the diagnostic interview,have a history of psychotic or bipolar disorders,and are receiving psychotherapy at the time of entering the study.Prescription medications for anxiety and depression lead to an exclusion if the dosage was changed one month before the beginning of the study.

### Randomization

Two hundred participants will be randomly assigned. The allocation list is produced by a random number generator Randlist [9] which randomly allocates participants in a 1:1 ratio with a block size of 8 to either IMI or WLC. The list is operated by an independent researcher not otherwise involved in the study. This researcher has no information about the participants other than the participants’s trial ID numbers and will randomize the participants in the order of the incoming informed consent form. During the randomization process, the allocation will be concealed from participants and researchers involved in recruitment. Participants will not be blinded to study conditions.

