### Procedure

Students who are interested in enrolling in the study will contact the study team through a contact form from a student mental health platform (i.e., on  www.studicare.com) or directly via email. If participants satisfy inclusion criteria they will be randomly assigned to either the IG or the WLC. Students who are assigned to the IG can initiate the online-based self-help intervention immediately after randomization. Students in the WLC will receive access to the program six months after randomization. The study includes three assessments: both groups are assessed at baseline (t0), immediately after completing the program (t1; 10 weeks) and at follow-up six months after randomization (t2). The assessment at t1 (10 weeks) is independent from treatment completion. Treatment adherence will be monitored after t1. Self-reported measures are collected using a secure web-based assessment system (UNIPARK, 256-bit encrypted [60]). This system allows for data validation (range checks, double data entries) to improve data quality. Additionally, participants’ SAD symptoms in IG will be assessed weekly via the intervention platform. The collected data will be stored securely.

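### A single published block size of 8 on one list leaves some assignments deducible if recruiting staff learn earlier ones; undisclosed, varying blocks would be a cheap improvement

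*Protocol article*

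**What the plan says.** The Randomization section of the protocol article gives the sample and the tool: "Two hundred participants will be randomly assigned", and "The allocation list is produced by a random number generator Randlist". The program "randomly allocates participants in a 1:1 ratio with a block size of 8 to either IMI or WLC". One list is described, with one block length. No stratification factor and no site-specific list is named.

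The list is worked through in sequence. The person operating it "will randomize the participants in the order of the incoming informed consent form".

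The article states three safeguards:

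- On the list holder: "The list is operated by an independent researcher not otherwise involved in the study". This person knows only trial ID numbers.
- On concealment: "During the randomization process, the allocation will be concealed from participants and researchers involved in recruitment".
- Under Diagnostic status, the interviewers who conduct the SCID at baseline and at 6 months are described as blind to condition, with four measures to keep them so.

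On the other side, "Participants will not be blinded to study conditions". The Procedure section makes the arm visible soon after assignment. "Students who are assigned to the IG can initiate the online-based self-help intervention immediately after randomization", while wait-list students get access six months later.

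**The concern.** Concealing the next line of a list does not conceal what can be deduced from the lines already used. If the block length is fixed and public and there is only one list, anyone who sees the completed assignments in order can count the position within the block. Once four of one arm have appeared, the rest of the block is known.

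The concealment statement is limited to the randomization step itself. The article does not say whether the staff who handle enquiries and consent forms learn each assignment afterwards. If they do, the order of incoming forms is a point at which knowledge of the list could matter.

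Selection bias is at stake. Both primary outcomes (SPS and SIAS) are self-reports by unblinded participants, compared with a wait-list, so unpredictable allocation is an important protection. The planned ANCOVA adjusts for the pre-score. It would not fully remove selection on traits that the pre-score does not capture, such as motivation to work through an unguided programme.

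**Working it through.** **The plan's own figure.** The article states no predictability figure. Its one calculable design figure is the sample size, which reproduces. With d = 0.4, one-sided alpha 0.025 and power 0.80, the normal approximation gives 99 per arm. The noncentral t distribution gives power 0.7997 at 99 and 0.8036 at 100 per arm. The stated 100 per group is correct, and the point below does not depend on it.

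**Inputs.** Allocation 1:1, block length 8 (so m = 4 per arm) and 200 participants, all from the Randomization section: 200 / 8 = 25 blocks.

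**Assumption.** The observer knows the block length, where blocks begin and every earlier assignment in order. The article does not establish that anyone does.

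**Certain assignments.** Each of the C(8,4) = 70 block patterns is equally likely. Position i is certain if one arm's four places were used in the first i − 1 positions, with probability 2 × C(i − 1, 4) / 70:

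| Position | Calculation | Probability certain |
|---|---|---|
| 1 to 4 | none possible | 0 |
| 5 | 2 × 1 / 70 | 2.9% |
| 6 | 2 × 5 / 70 | 14.3% |
| 7 | 2 × 15 / 70 | 42.9% |
| 8 | 2 × 35 / 70 | 100% |

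The sum is 112 / 70 = 1.6 per block, which agrees with 2m / (m + 1) = 8 / 5. This is 1.6 / 8 = 20%, or 25 × 1.6 = 40 of 200.

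**Correct guesses.** The observer always names the arm with more places left, and ties count one half. Expected correct guesses per block = m − 1/2 + 2^(2m−1) / C(2m, m) = 4 − 0.5 + 128 / 70 = 5.329. That is 5.329 / 8 = 66.6%, or about 133 of 200, against 100 by chance.

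**Alternatives.** These were simulated for trials of 200. For the mixed blocks, the sizes are equally likely and the observer knows the set of sizes but not their order.

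| Scheme | Certain | Guessed correctly |
|---|---|---|
| Fixed 8 | 20% | 66.6% |
| Random 4, 6, 8 | about 2% | about 68% |
| Random 8, 12, 16 | about 2% | about 64% |
| Big-stick, limit 10 | about 4% | about 52% |

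Hiding and varying the block length removes nearly all the certainty. It does little to the guess rate, and adding blocks smaller than 8 makes the guess rate worse.

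**Cost in power.** If recruitment stops inside a block of 16, the worst split is 8 apart (96 against 104). The noncentral t distribution gives power 0.8030, against 0.8036 at 100 per arm. The big-stick limit allows at most 95 against 105, with power 0.8027.

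**The case against.** The strongest reply is that the article puts nobody in a position to use this knowledge. The list holder is outside the study and sees only ID numbers. Recruiting researchers are covered by the concealment statement. The SCID raters, who hold the diagnostic discretion at entry, are described as blind. The other entry criteria are mostly questionnaire cut-offs, and students refer themselves. The programme is online with automatic messages, so no therapist contact reveals the arm. To exploit the list, staff would have to track the whole sequence across recruitment in three countries and hold back or reorder consent forms. A block of 8 is also less guessable than smaller blocks, and the Randomization section contains no error or contradiction.

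Most of this stands, and it is why the point is minor. Two gaps remain. Concealment is stated only for the randomization step. The blinding measures for raters concern the condition of the person being interviewed, so they do not address what other recruiting staff know about participants already assigned.

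A reader might infer that recruiting staff do see the running sequence. The article does not say so: it shows that participants learn their arm, and it is silent on staff.

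A reader might also turn the guess rate into a bias. If each guess shifted the expected outcome by 0.1 SD in the favoured direction, the difference would be 0.1 × 2 × (2 × 0.666 − 1) = 0.066 SD, and an unadjusted t-test with 100 per arm would reject about 6.7% of the time under no effect. The article does not support that as an estimate. The 0.1 SD has no source, every guess must be acted on in both directions, and the planned ANCOVA is ignored.

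**Conclusion.** The concern holds as a minor design weakness. The article fixes and publishes one block length of 8 on one list, in a trial with unblinded participants, and its concealment statement does not extend to completed assignments. For someone who knew the full earlier sequence, 20% of assignments would be certain and 66.6% guessable. Both figures are exact under that condition and are upper limits otherwise.

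The conclusion rests on two readings of a condensed article. One is that there are no strata, because none is named. The other is that staff knowledge of completed assignments is not excluded, because nothing excludes it. It does not show that selection occurred or that the type I error rate is inflated.

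**What to change.** For any assignments not yet made, have the independent researcher generate the rest of the list with randomly varying block sizes of at least 8, for example 8, 12 and 16. Keep the sizes from the study team and out of public documents, and report them after recruitment closes. In the Randomization section, replace the stated block size with a sentence saying that sizes vary and are undisclosed. Do not add sizes below 8.

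The cost is one regenerated list, one sentence and a slight possible final imbalance with negligible loss of power. No extra participants or procedures are needed.

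A big-stick rule with limit 10 (a coin toss unless the imbalance reaches 10) is an optional alternative if a lower guess rate is wanted. It is a design preference and not a required correction. If all assignments have already been made, nothing in the list can be changed; the trial report should then state the block size and whether recruiting staff knew completed assignments.

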### Internet-based self-help intervention with an additional session on fear of positive evaluation

The intervention is based on the well-established cognitive-behavioral treatment of Clark and Wells (1995) [51] and has been shown to be efficacious in several previous studies [27, 52–55]. It consists of nine text-based sessions, various exercises (e.g. attention training) and diaries (such as a diary to identify and question negative thoughts). Participants are advised to complete one session per week, review the exercises, and complete diaries. The approximate time required to complete one session is 60 min, and participants are encouraged to practice the strategies in their daily life. An overview of the sessions is summarized in Table 1. The original intervention was tailored to the university setting, for example, by providing case examples of socially anxious students.

**Table 1 Tab1:** Session content for the SAD internet-based self-help program

Session	Intervention content
Session 1 Motivational enhancement	Reasons to initiate change, defining goals and recoding introspection of difficult social situations with help of an anxiety protocol
Session 2 Psychoeducation	Information on SAD and maintaining factors such as negative thoughts, safety behaviors and self-focused attention
	Development of an individual model for SAD
Session 3 Cognitive restructuring	Identification and modification of negative thoughts (dysfunctional assumptions) with the help of a thought diary
Session 4 Fear of positive (social) evaluation	Information about FPE (examples and explanatory models)
	Identifying FPE using a diary
	Recognizing the devaluation of own achievements, the benefit and the risks of positive evaluation using a diary
	Endorsing positive evaluations and emotions applying a self-compassion-interventions
Session 5 Self-focused attention	Various exercises to reduce self-focused attention
Session 6 Behavioral experiments	Planning and conducting in-vivo exposures
Session 7 Summary and revision	Summary of the key elements of the training
	Highlighting the importance of revising the exercises (e.g. in-vivo exposure)
Session 8 Healthy lifestyle and problem solving	Information about healthy lifestyle (e.g. sports, nutrition)
	Conveying problem solving skills
Session 9 Relapse prevention	Strategies to maintain the acquired skills
	Preparing for possible relapses

An additional module in session 4 not part of the original Clark and Wells program targets FPE. FPE is defined as discomfort and fear in reaction to positive feedback from others. The module contains psychoeducational material regarding the definition and etiology of FPE according to the bivalent fear of evaluation model [43] and the evolutionary model [44], as well as information on FPE-related cognitive strategies such as the disqualification of positive social outcomes (DPSO). A thought diary is introduced to identify and modify FPE-related cognitions, including perceived costs and advantages of positive evaluation. Additionally, the module contains exercises that aim at promoting self-compassion as well as the experience and acceptance of positive emotions which have been linked to a decrease of FPE [56].

Although this is a therapeutically unguided self-help intervention, guidance is provided via standardized automatic messages aiming to promote adherence. Adherence reminders follow procedures used in a number of previously conducted studies [57–59]. They consist of one positive reinforcement per session completion and one automatic reminder if participants do not log into the platform for more than one week. These automated reminders contain standardized personalized motivational messages, which strengthen participants’ adherence to the intervention.

